## Variables

### Functional capacity and postural balance

*Tinetti Test: balance and gait assessment*: The Tinetti Test (TT) assesses balance (sitting and standing) with 14 items (score out of 24) and gait with 10 items (score out of 16), resulting in a total score out of 40. Higher scores indicate better performance. The test showed good interrater reliability and concurrent validity [31,32].*Unipedal Stance Test:* The Unipedal Stance Test (UPST) measures static balance ability [33]. It can be conducted with eyes open and closed. Participants must remain in unipedal for 10 seconds on each side, first on the dominant side and then on the non-dominant side. After 30 seconds of recovery, the test is repeated on the opposite side.*Time Up and Go test:* The Time Up and Go test (TUG) measures the time it takes for a subject to stand from a chair, walk three meters, turn around, and sit down again. Times begin when the subject stands up and stops when seated [34,35].*Balance Assessment Using the Nintendo Wii Console:* This includes the one leg balance test and center of gravity assessment, as well as Romberg Test variants: Eyes Open (REO), Eyes Closed (REC), and on Foam Pad (RuFP), as performed in the posturography test. The Nintendo Wii provides accurate measures of body center of pressure (COP), an important metric for balance stability assessment approximating the body’s center of mass. The Romberg test assesses gait disturbance caused by abnormal proprioception, disequilibrium from central vertigo, and peripheral vertigo [36]. Patients are asked to stand with feet together, arms next to the body, first with eyes open and then closed. The patient tries to maintain his balance. The test is scored by counting the seconds the patient can stand with eyes closed.*Posturography:* Static posturography is performed in four different situations using the Romberg test and stability limits with the NedSVE/IBV^®^ platform [37]. Postural stability is quantified using the Dinascan/IBV force platform (600 × 370 mm of active area, 100 mm in height and 25 kg in weight) with the NedSVE/IBV^®^ system. Participants find the most stable position while barefoot, with relaxed arms and feet at a 30° angle. Four static conditions are measured, each lasting 30 seconds. Conditions: Romberg test with eyes open (ROA), Romberg test with eyes closed (ROC), Romberg test with eyes open on a foam pad (RGA), and Romberg test with eyes closed on a foam pad (RGC).

Stability limits are assessed by maximum anteroposterior (AP) and mediolateral (ML) displacement (mm), representing the furthest point reached by the centers of pressure in the anteroposterior and mediolateral axes during the recording time. Posturography evaluates whether there is a BD and in which component it occurs (visual (VIS), vestibular (VES), or somatosensory (SOM) [37].

The balance assessment is based on the comparison of the parameters that best discriminate the pathology of the general population with those obtained from patterns of normality segmented by age (database of the Institute of Biomechanics of Valencia). Ratings are displayed in percentages, so that results other than 100% reflect discrepancy with respect to normal values. It is considered pathological when the results are less than 95%, indicating that these subjects are more likely to present a disorder in the studied system. Pathological values for the limits of stability are considered to be below 85% [37].

*Short Physical Performance Battery (SPPB)* [38]*:* The Short Physical Performance Battery is an objective tool for measuring functional capacity, balance, and lower limb strength in adults over 65. The test includes three domains to assess functional mobility: gait, sit-to-stand, and balance. A score below 8 indicates mobility and physical exercise limitations and is associated with a higher risk of mobility disability and, consequently, a higher risk of falls. A score of 8 or higher is considered within the normal range*.**Muscle Strength of Lower Limbs*: Maximal isometric muscle strength of knee extension following the protocol described by Gandevia [39].*Gait Speed:* Measured over 6 meters or 2.44 meters if the participant reports walking slowly.*Functional capacity* was assessed using the *Lawton-Brody IADL scale* [40]*.* This scale assesses instrumental activities of daily living (IADLs), which measure a person’s ability to live independently. It includes tasks such as managing finances, shopping, using the telephone, and handling transportation. *The Barthel ADL index* is a scale that measures basic activities of daily living (ADLs), assessing a person’s ability to perform essential self-care tasks such as bathing, dressing, toileting, transferring, and eating*.**Physical activity measured using the abbreviated Spanish version of the Minnesota Leisure-Time Physical Activity Questionnaire (VREM)* [41]*:* The VREM is a short Spanish version of the Minnesota Leisure Time Physical Activity Questionnaire (CAFM). It is a tool designed to assess the quality and quantity of physical activity during leisure time. It consists of six items that evaluate physical activity carried out in the past month, considering only activities performed during leisure time.

### Health assessment tool

Physical function is assessed by measuring gait speed.Functional cognitive status is determined using the Mini-Mental State Examination (MMSE), with a score ranging from 0 (the worst outcome) to 30 (the best).Chronic morbidity is evaluated by counting the number of diagnosed chronic conditions. Diagnoses, based on the ICD-10 system, are gathered from the patient’s electronic medical record.Mild disability is measured using the Lawton-Brody scale, assessing instrumental activities of daily living (IADLs) that the individual can not perform independently. Four activities will be included in the analyses: shopping, managing finances, using the telephone, and using public transportation. Household tasks are excluded to avoid gender-related biases.Severe disability is defined as the number of basic activities of daily living (ADLs) that the person can not perform independently. ADLs, assessed using the Barthel Index, will include five essential self-care activities: bathing, toileting, transferring, and eating.

### Covariables

*Short Falls Efficacy Scale International:* The Short Falls Efficacy Scale International (Short FES-I) is the abbreviated version of the FES-I, measuring fear of falling. It includes seven of the sixteen FES-I items, assessing how likely the participant believes they might fall in seven daily situations [42]. Responses range from 1 to 4: not at all concerned, somewhat concerned, fairly concerned, or very concerned. The total score ranges from 7 to 28, with higher scores indicating worse fear of falling [43].Record of falls and consequences during the year prior to study inclusion.Charlson Comorbidity Index, number of chronic conditions, and specific chronic comorbidities (ICD-10).Cognitive capacity assessed using the *Pfeiffer* short portable mental status questionnaire or *Mini Mental State Examination*.Standard eye acuity test.Subjective assessment of sense organs (visual/auditory): normal, mild impairment, or severe impairment.Need for technical assistance when walking (yes/no), and type of assistance used.Record of rehabilitation gait treatment in the past year.Loneliness: measurement of loneliness using the *UCLA-3 Loneliness Scale* and the *Jong Gierveld Loneliness Scale*.Blood sample for a future study of frailty/sarcopenia biomarkers. Aging is associated with increased proinflammatory cytokines. Elevated cytokines levels are also observed in sarcopenia, obesity, and osteoporosis (increased levels of IL6 and low levels of IGF-1), as well as other endocrine biomarkers (low dehydroepiandrosterone sulfate, vitamin D and leptin).Other variables: Affiliation data, numerical ID code, anthropometric measurements, regular drug treatment, socioeconomic status (education, financial level, civil status), and lifestyle factors (smoking habits, alcohol consumption.

### Retinography

Using a non-mydriatic camera, retinal images were obtained from each eye without pupillary dilation, capturing both central and nasal views. These images were then analyzed with the IMEDOS Vessel Map software (IMEDOS Systems UG, Germany), while the Tortuosity Index and A/V ratio were measured with the retinal analysis platform of the VARPA group from the University of A Coruña.

### Cohort follow-up

Record of falls (indicating place and activity at the time) and consequences: contusions, fractures, hospitalization, or death within 30 days.Formal and informal social care (self-reported, hours/month).Hospital admissions, 30-day readmission, days spent in the hospital, primary care visits, and specialist care visits.

The same variables collected at baseline will be gathered again at the final follow-up visit.

### Data collection

A standardized data collection protocol and logbook will be established following a pilot test on 50 cases. All information and data collection will be conducted using an electronic form designed with RedCAP. This pilot test aims to detect design errors, train recruiters, and verify consistency in data collection to ensure a standardized process. A random sample of candidate subjects will be selected and contacted (up to six attempts on different days and times). With prior knowledge of their referring doctor or nurse, these candidates will be invited to participate in the study. An informative visit will be scheduled to review inclusion and exclusion criteria and to sign the informed consent form.

If included in the study, the complete baseline visit will be conducted at this time, except for the blood test, which will be scheduled within one month from inclusion. From this baseline visit, subjects will be followed up to detect falls by using: a) personal calendar for recording falls, and b) bimonthly phone calls.

The final visit will be conducted at 18 months, during which balance will be assessed again through clinical tests, retinography, and posturography. The detailed schedule for enrollment, interventions, and assessments is presented in the SPIRIT diagram (Fig 1). A flowchart illustrating the overall study protocol and participant flow is provided in Fig 2.

**Fig 1 pone.0346698.g001:**
[figure not shown]
SPIRIT diagram illustrating the schedule for enrolment, interventions, and assessments.

**Fig 2 pone.0346698.g002:**
[figure not shown]
Flowchart of the study protocol and participant assessments.

### Statistical analysis

Qualitative variables will be summarized as absolute and relative frequencies. Continuous variables will be described using mean and standard deviation or median and interquartile range, as appropriate. Distributional assumptions will be assessed using graphical methods, and the Shapiro-Wilk test will be used to check for data normality. Baseline characteristics between participants with and without balance disorders (BDs) will be compared using the Chi-square or Fisher’s exact test for categorical variables, and the Student’s t-test or Mann-Whitney U test for continuous variables, based on the distributional properties of the data.

BD prevalence and cumulative incidence at 18 months will be estimated with 95% confidence intervals (CIs). The association between BDs and the occurrence of at least one fall during the 18-month follow-up will be analyzed using a modified Poisson regression with robust variance to estimate relative risks (RRs) and 95% CIs. Additionally, a survival analysis for the time until the first fall will be performed using Kaplan-Meier survival curves and Cox regression.

To evaluate the predictive capacity of knee extensor strength and the composite physical-cognitive score for BDs and fall risk, separate multivariable modified Poisson regression models with robust variance will be constructed. Continuous predictors will be modeled as such, and adjusted RRs with 95% CIs will be reported. The diagnostic performance of the Wii Balance Board™ will be evaluated against posturography (gold standard) by calculating sensitivity, specificity, predictive values (PPV, NPV), likelihood ratios, and the area under the ROC curve (AUC). For the validation of the Health Assessment Tool (HAT), we will compare baseline values with those obtained at the 18-month follow-up. The predictive capacity of the HAT scale for BDs and health services utilization (e.g., hospital admissions, primary care visits) will be estimated by computing the AUC.

The analysis regarding retinal microvasculature (Aim 2) will be treated as an exploratory analysis. While we investigate the link between retinal vascular health and BDs using modified Poisson regression adjusted for predefined clinical confounders, this component primarily aims to identify potential new non-invasive biomarkers. Therefore, findings related to these parameters will be interpreted as hypothesis-generating for future research rather than primary confirmatory outcomes.

A two-sided p-value <0.05 will be considered statistically significant. All analyses will be performed using SPSS version 23.0.

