## Methods

### Study design

This study will be performed and reported according to the Strengthening the Reporting of Observational Studies in Epidemiology Criteria (STROBE) [29].

This is a two-phase, observational study:

Phase 1: A descriptive, cross-sectional study on the prevalence of BDs in individuals aged 65–72.

Phase 2: A longitudinal, population-based cohort study to determine the occurrence of postural BDs and their consequences over an 18-month follow-up period in individuals aged 65–72. The potential consequences include: a) Falls: Defined as involuntary events in which an individual loses their balance and ends up on the floor or another hard surface. b) Fall-related consequences: Including contusions, fractures, hospitalization, and death.

Based on the above-mentioned cohort data, the external validation of the HAT scale will be performed by analyzing its predictive capacity for BDs and the use of health services after 18 months of follow-up (hospital admissions, 30-day readmissions, days spent in the hospital, primary care visits, and specialist care visits).

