### Participants

The target population is an age-based cohort of people aged 65–75 living in Mataró. This age range was selected to find individuals who do not yet have BDs, enabling the calculation of the incidence. According to the 2017 municipal register, and the population’s age structure, there are 2,215 people in this age range. A total of 1,316 people will be randomly selected from the Primary Care Information System (SIAP) database, which includes health cardholders and covers nearly the entire population. The selection process will be conducted using a computer-generated random sequence to form a sample stratified by gender and age. Our research team will contact the selected participants using the phone numbers registered in the SIAP and invite them to participate. To ensure robustness and minimize non—response bias, a protocol of up to six call attempts on different days and at different times will be implemented for each candidate before considering them unreachable.

Eligibility criteria: 1) Aged 65–75 years at the time of recruitment. 2) Resident of Mataró (Barcelona, Spain) and registered in the Primary Care Information System (SIAP). 3) Able to walk independently, defined as the ability to walk at least 10 meters without the assistance of another person, although the use of technical aids (e.g., cane, walker) is permitted.

Exclusion criteria: 1) Permanent inability to walk or requirement of human assistance for mobility. 2) Terminal illness, as a document in the primary care electronic medical record. 3) Severe cognitive decline, as assessed by the Pfeiffer questionnaire or Mini-Mental State Examination (MMSE) during the initial evaluation, or a known diagnosis of advanced dementia. 4) Significant language barrier that prevents the completion of clinical scales or understanding of study procedures. 5) Lack of phone access for follow-up calls.

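### Aim 4 judges prediction by risk ratios alone, and part of the HAT validation (a before-after comparison, and AUC for visit counts) does not measure prediction

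*Protocol article*

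**What the plan says.** Study aims lists, among the primary aims, whether knee extensor strength and a composite of physical and cognitive function can predict BDs and fall risk. For this, Statistical analysis plans separate multivariable modified Poisson models and fixes the output: "Continuous predictors will be modeled as such, and adjusted RRs with 95% CIs will be reported".

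The secondary aim is external validation of HAT. Study design defines it by prediction: "the external validation of the HAT scale will be performed by analyzing its predictive capacity for BDs and the use of health services". Statistical analysis gives two steps. The first is that "we will compare baseline values with those obtained at the 18-month follow-up". The second is an AUC for BDs and for service use: "health services utilization (e.g., hospital admissions, primary care visits) will be estimated by computing the AUC".

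The service-use outcomes are listed under Cohort follow-up: "Hospital admissions, 30-day readmission, days spent in the hospital, primary care visits, and specialist care visits".

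On the HAT inputs, Health assessment tool says the basic activities "will include five essential self-care activities: bathing, toileting, transferring, and eating".

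**The concern.** Three analyses are described as prediction or validation, but the stated method gives something else.

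- **Aim 4.** An adjusted risk ratio can be highly significant while the measure hardly separates those who fall from those who do not. Under the two-sided 0.05 rule, a primary aim could then be reported as successful prediction on association alone. The Discussion also says the goal is to find the markers that best predict falls. Risk ratios for continuous predictors on different scales, from separate models, cannot rank markers.
- **HAT before and after.** Comparing a score at two visits shows how the cohort moved. It relates the score to no outcome, so it cannot support the validation that Study design describes.
- **AUC for counts.** An ROC AUC needs a yes/no event. Visits and hospital days are counts, so the result depends on a cut-off that the article does not give.

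**Working it through.** No figure in the article is disputed. The check sets question against method, then illustrates the two places where size matters.

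**1. Question against method**

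| Item | Question | Stated method | Match |
|---|---|---|---|
| Wii board | Agreement with posturography | Sensitivity, specificity, predictive values, likelihood ratios, AUC | Yes |
| Knee strength, composite (Aim 4) | Can they predict BD and falls? | Adjusted risk ratios only | Association only |
| HAT, step 1 | Predictive capacity | Baseline versus 18-month values | No outcome involved |
| HAT, step 2: BD; admission or readmission as yes/no | Predictive capacity | AUC | Yes (discrimination) |
| HAT, step 2: primary care visits, specialist visits, hospital days | Predictive capacity | AUC | Needs an event definition |

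Three of the five service-use outcomes are in the last row.

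**2. A significant risk ratio with weak discrimination**

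Inputs from Sample size: 1,316 people and 20% dropout, so 1,316 × 0.8 ≈ 1,053 followed; outcome risks p of 33% (expected baseline BD prevalence), 38.5% and 50% (assumed fall incidences). Assumed here: a standard normal predictor x and risk = min(1, exp(a + x·ln RR)), with a set so that the mean risk is p. The AUC comes from simulating one million people.

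Approximate test statistic: z = ln(RR) / √[(1 − p)/(p·n)].

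For p = 0.33 and RR = 1.2: the standard error is √[0.67/(0.33 × 1,053)] = 0.0439, and z = 0.1823/0.0439 = 4.15.

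| RR per SD | p = 33%: z, AUC | p = 38.5%: z, AUC | p = 50%: z, AUC |
|---|---|---|---|
| 1.2 | 4.15, 0.577 | 4.68, 0.584 | 5.92, 0.602 |
| 1.3 | 5.98, 0.609 | 6.74, 0.620 | 8.51, 0.646 |
| 1.5 | 9.23, 0.668 | 10.41, 0.682 | 13.16, 0.717 |

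An RR of 1.2 far exceeds 1.96 in every column, while its AUC stays at about 0.58 to 0.60 (0.50 is chance). The z values ignore covariate adjustment. The article gives no expected BD incidence, so the 33% column illustrates BD by its prevalence only.

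**3. The AUC for a count depends on the cut-off**

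Assumed here, since the article gives no visit rates: a mean of 8 visits at the average HAT value, gamma-Poisson overdispersion (shape 2), and a fixed log-rate effect of 0.4 per SD of HAT.

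| Event | Share with event | AUC |
|---|---|---|
| ≥ 1 visit | 95.3% | 0.675 |
| ≥ 5 | 63.9% | 0.682 |
| ≥ 10 | 33.6% | 0.716 |
| ≥ 15 | 17.3% | 0.754 |
| ≥ 20 | 9.0% | 0.793 |
| ≥ 30 | 2.6% | 0.855 |

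The same score with the same effect yields an AUC from 0.68 to 0.86, depending only on where the count is cut.

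**4. The ADL list**

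Health assessment tool announces five activities and names four. The Barthel description under Functional capacity and postural balance names five, including dressing.

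**The case against.** A reader might infer that none of these analyses answers its prediction question. The text does not support that. Posturography has fixed pathological thresholds, so BD is yes/no, and admission and readmission can be too. For these the HAT AUC is a proper measure of discrimination.

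The before-after comparison can also be defended as a check of responsiveness: the article credits HAT with detecting health changes early and with sensitivity to functional decline. That is a fair use. But the sentence is introduced as validation and states no such purpose, while Study design ties validation to prediction.

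On counts, event definitions may stand in an analysis plan that is not shown, so this is the weakest part. Nothing in the article says that cut-offs would be chosen after seeing the data, or that nearly everyone would have a primary care visit. What stands is that AUC is the only method named for a quantity that a cut-off partly discards.

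On Aim 4, the Abstract says only that the study will explore whether the measures can serve as predictors, and risk ratios address that in a loose sense. The primary aim and the analysis text, however, both speak of prediction. If the composite is HAT itself, which the article does not say, the planned AUC would cover BD but not falls, and knee strength would still have none.

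Two inferences about the HAT inputs also go too far. Pfeiffer or MMSE is accepted for exclusion screening and as a covariate, but the HAT section itself assigns the MMSE, and nothing says that any participant will lack one. The four-item ADL list is most likely an omitted word; the Barthel Index is collected, so no data are lost.

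**Conclusion.** The point holds in this limited form. Aim 4 has no stated measure of discrimination, although the same paragraph uses one for the other two tools; as a primary aim, this is the main part. The HAT before-after comparison is description presented as validation. For visits and hospital days, AUC is a poorer choice than a count model and is undefined without an event. The HAT analysis for BD, admission and readmission is sound as far as discrimination goes.

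The mismatch of question and method rests on the article's text alone. The sizes (AUC of 0.58 to 0.60 at an RR of 1.2; AUC of 0.68 to 0.86 across visit cut-offs) rest on assumed distributions and show what can happen, not what this cohort will give. The ADL mismatch is a minor correction.

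**What to change.** - **Aim 4.** Keep the risk ratios. Beside them, report the AUC (or the C-index for time to first fall) with a 95% CI, for knee strength and for the composite, and the gain over a model with age, sex and prior-year falls. Correct the multivariable figures for optimism, for example by bootstrap.
- **HAT before and after.** Keep the comparison, but label it as a description of change over time.
- **HAT validation.** Relate baseline HAT to later outcomes. Use AUC with a 95% CI for binary ones: incident BD among those free of BD at baseline, any admission, and readmission. For primary care visits, specialist visits and hospital days, use a count model such as negative binomial with a follow-up-time offset, and report the rate ratio per HAT point.
- **ADL items.** Reconcile the stated five with the four listed.

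The cost is revised wording and a few more models. Falls in the prior year, visits and hospital days are already in the data collection, and Study status says that no analysis had begun.
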